### Control group 2: care as usual by GP

Participants from control group 2 are referred to their own GP for smoking cessation treatment. They are asked to make an appointment with their GP within the next ten days. They are provided with a referral letter explaining to the GP that the person is participating in a study on smoking cessation. This letter does not give any information about the results from spirometry and the fact that the participant has airflow limitation. The GP is asked to provide the care he/she usually provides to patients who want to quit smoking. In the Netherlands, primary "care as usual" for smoking cessation involves the use of a protocol for low intensity health education and promotion, the so-called "H-MIS" [22]. According to the protocol of the H-MIS, the GP and/or the assistant takes the following steps to assist the smoker during a quit attempt: determine the smoking profile of the smoker, determine the motivation to stop smoking (and increase the motivation if necessary), talk about the barriers of quitting smoking, set a target quit date, discuss the use of smoking cessation aids, and arrange follow-up. A semi-structured interview will be used among participants from control group 2 during the first follow-up visit (day 50) in order to assess whether participants have consulted their GP and which treatment for smoking cessation the GP has delivered.

Neither participants from control group 2 nor their GP will be informed about the results from spirometry and the detected airflow limitation. However, if a GP explicitly requests the results from spirometry they will be provided (see further paragraph "ethical considerations").

### Use of nortriptyline for smoking cessation

Previous research has shown that the combination of counselling and pharmacotherapy is more effective than either alone [31-33] and international guidelines recommend the use of pharmacotherapy in all patients trying to make a quit attempt [21,34]. Participants from both the experimental group and control group 1 receive an equal dosage of nortriptyline (Nortrilen^®^) for smoking cessation. Nortriptyline is a tricyclic anti-depressant which has been shown to be a cheap and effective alternative for the anti-depressant bupropion (Zyban™) [31,35]. Participants start taking nortriptyline on the day of the first counselling visit (FC1, day 1) in which they receive instructions about the use of nortriptyline by the RN. A run-in period of 10 days until the TQD is needed to achieve steady-state blood levels of nortriptyline. From day 1 through day 3, participants take one pill of 25 mg nortriptyline once a day (preferably after dinner). From day 4 through day 7, participants take 50 mg a day (given as two pills of 25 mg). As from day 8 through the end of the treatment period (day 49), participants take 75 mg a day (given as three pills of 25 mg). The RN monitors the correct use of the medication and the occurrence of side-effects during the intervention period. In case of unpleasant or severe side-effects, the dosage will be reduced or the use of the medication will be stopped. At the first follow-up visit (day 50) the RA collects and counts the remaining pills.

### Follow-up visits

Three follow-up visits for all participants are scheduled at day 50 (approximately five weeks after the TQD), day 197 (approximately six months after the TQD), and day 379 (approximately twelve months after the TQD; see also figure 1). The TQD in participants from control group 2 is set at 8 weeks after the day participants were randomized and informed about group allocation. We estimated that this would be sufficient time to schedule a consultation with the GP and to prepare stopping smoking, and that the time lag between day of randomization and TQD would be about the same compared to the experimental group and control group 1 (in the latter groups, we account for a delay between day of randomization and start of treatment). Participants receive a reminder letter including a follow-up questionnaire and a cost-diary seven weeks prior to all three visits. The RA calls every participant one week prior to the visit to confirm the appointment. Minor deviations from the scheduling of follow-up visits will be allowed in order to retain as many participants in the study as possible.

At every follow-up visit, participants hand in their questionnaire and cost-diary. The RA briefly discusses the quit attempt. Urine is collected from every self-reported non-smoker for the analysis of cotinine levels.

During the final follow-up visit, spirometry is repeated in all participants. All spirometric outputs are carefully evaluated by a pulmonologist (GW) and reported to the participant's GP by letter. All participants are asked to consult their GP for information about their lung function and further treatment.

### Data collection

An overview of all measurements per visit is given in table 1. The paper-and-pencil questionnaires are filled out at home by the participants and are handed in during the visits. Completion of the questionnaires takes about 30 minutes. Data from the questionnaires will be double-entered and checked by blinded assistants from the centre for data and information management of Maastricht University (MEMIC).

**Table 1 T1:** Overview of measurements per visit

**Measurement**	**Baseline visit**	**Follow-up visit 1 (day 50)**	**Follow-up visit 2 (day 197)**	**Follow-up visit 3 (day 379)**
Demographic characteristics	•			
Smoking:				
Tobacco use and quit attempts [41]	•	•	•	•
Fagerström Test for Nicotine Dependence (FTND) [42]	•			
Health perception: (self-constructed questions)				
health concerns	•	•	•	•
risk perception	•	•	•	•
self-exempting beliefs	•	•	•	•
Respiratory health complaints:				
COPD diagnostic questionnaire [43, 44]	•			
Medical Research Council (MRC) dyspnoea scale [45, 46]	•		•	•
Clinical COPD Questionnaire (CCQ) [47, 48]	•	•	•	•
Health-related quality of life:				
EuroQol (EQ-5D) [39, 40]	•	•	•	•
Short-form 36-item questionnaire (SF-36) [49, 50]	•	•	•	•
Chronic Respiratory Questionnaire self-reported (CRQ-SR) [51, 52]	•	•	•	•
Mental health:				
Beck Depression Inventory (BDI) [53]	•	•	•	•
Hospital Anxiety and Depression Scale (HADS) [54–56]	•	•	•	•
Cost diary: measurement of direct en indirect medical and non-medical costs [38]		•	•	•
Physical measurements:				
Physical height and weight	•	•	•	•
Post-bronchodilator spirometry	•			•
Urine cotinine (only in self-reported quitters)		•	•	•

Urine is collected from every self-reported non-smoker during each follow-up visit to validate non-smoking. The urine is kept in a 100 mL plastic cup with a screw cap and temporarily stored in a refrigerator for a maximum of seven days before delivery to the laboratory of the Department of Health Risk Analysis and Toxicology (GRAT) of Maastricht University. The concentration of cotinine in urine is measured by a highly specific radioimmunoassay using monoclonal antibodies [36]. The reagents for the assay are obtained from the Department of Biochemistry, Brandeis University, Massachusetts, USA.

The analysts assessing the urine cotinine levels and all assistants entering data from questionnaires are kept blind to the group allocation of participants.

### Data analysis

The primary outcome measure is prolonged abstinence from smoking during a period of 12 months after the TQD. Prolonged abstinence is defined as follows: abstinent from smoking at all three follow-up visits; at day 50 (approximately 5 weeks after the TQD), day 197 (after six months), and day 379 (after 12 months). Participants are allowed to miss the second follow-up visit (day 197) if they have been abstinent from smoking at the first (day 50) and the last follow-up visit (day 379; interpolation). A participant is defined as abstinent from smoking at a follow-up visit if both of the following two conditions are met:

1. urine cotinine level < 50 ng/mL [37] and

2. self-reported quitter, not having smoked a single cigarette since stopped smoking.

All randomized subjects will be included in the analysis and subjects not showing up at the follow-up visit or with a missing value on one of the two above measures are regarded as smokers (intention-to-treat analysis). Statistical difference in primary outcome will be analyses using Chi-square tests.

The secondary research questions will be analysed as follows (see the last paragraph of the introduction for an overview of all secondary research questions).

1. Baseline predictors of outcome will be analysed by regressing the primary outcome measure (12-month prolonged abstinence) on candidate predictors measured at baseline (such as age, sex, airflow limitation, previous quit attempts, or nicotine dependence) in a multivariate logistic regression model, controlling for treatment group.

2. The health effects of smoking cessation will be analysed by regressing measures of lung function, perceived specific health-related complaints, quality of life, and mental health on abstinence at each follow-up visit using linear regression models.

3. The cost-effectiveness and cost-utility of early detection of airflow limitation in combination with smoking cessation will be analysed using data from the cost diaries [38]. Participants fill out these diaries during three periods of six weeks each: during the intervention until the first follow-up visit (day 50), during the period until the second follow-up visit (day 197), and during the period until the last follow-up visit (day 379). The economic evaluation is based on direct medical costs (e.g. treatment costs, spirometry), direct non-medical costs (e.g. reimbursement of travelling expenses), and on indirect costs (e.g. sickness absence), which are related to respiratory complaints. Effects are measured in physical units (such as number of successful quit attempts, FEV_1_) and Quality Adjusted Life Years (QALY'S) are measured with the EuroQol (EQ-5D) [39,40].

4. The effects of labelling of disease (COPD) will be analysed by mediation and moderation analyses using linear and logistic regression models. The outcome variable in these analyses is abstinence from smoking at the first follow-up visit. Only data from the experimental group and control group 1 will be used.

5. The ethical considerations of early detection of airflow limitation will be analysed in a qualitative analysis using data from the ethical exit interviews which are performed in participants attending the last follow-up visit.

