### Sample size calculation

The primary research question aims at a contrast in efficacy between the experimental group (confrontational counselling) and control group 1 (health education and promotion). Therefore, the calculation of the sample size is based on the identification of a difference in proportion of prolonged abstinence after 12 months between these two groups. We estimated the relevant difference in proportion to be 15%: 35% quitters in the experimental group versus 20% quitters in control group 1. When putting the risk of a type I-error at 5% and the risk of a type II-error at 20%, 136 participants per group are needed at onset to detect a difference in proportions of 15%. Considering 10% lost to follow-up, 150 participants per group are needed in the experimental group and control group 1 (136 × 0.9^-1^). We expect a larger difference between the experimental group (35%) and control group 2 (8% [22]). Therefore, less participants are needed in control group 2. We used a formula for the calculation of sample sizes of unequal groups and set the ratio between the experimental group and control group 2 at 3:1. This resulted in a minimum of 32 participants in control group 2 (taking into account 10% lost to follow-up).

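### The primary abstinence comparison is a valid but unadjusted chi-square test; adjusting for a short, pre-fixed list of baseline variables already collected would be a cheap gain in precision

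*Protocol article*

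**What the plan says.** All references are to the protocol article.

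- **Outcome** (Data analysis): "The primary outcome measure is prolonged abstinence from smoking during a period of 12 months after the TQD". It is binary. Everyone randomised is analysed, and a missed visit or missing measure counts as smoking.
- **Test** (Data analysis): "Statistical difference in primary outcome will be analyses using Chi-square tests". No adjusted analysis of the treatment effect is named.
- **Primary contrast** (Sample size calculation): experimental group against control group 1, with "35% quitters in the experimental group versus 20% quitters in control group 1". The calculation gives "136 participants per group are needed at onset to detect a difference in proportions of 15" percentage points, then "Considering 10% lost to follow-up, 150 participants per group are needed in the experimental group and control group 1".
- **Allocation** (Randomization and planning procedure): blocks of seven in the ratio 3:3:1, with no stratification factor named.
- **Baseline data** (Data collection, Table 1): demographics, tobacco use and quit attempts, the Fagerström score (FTND) and post-bronchodilator spirometry are all recorded at the baseline visit.
- **Use of those data** (Data analysis, secondary question 1): a logistic model of the same 12-month outcome uses "candidate predictors measured at baseline (such as age, sex, airflow limitation, previous quit attempts, or nicotine dependence", while controlling for treatment group. Its stated purpose is to find predictors.

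**The concern.** As described, neither the allocation nor the primary analysis uses any prognostic information about the participants. The plan nevertheless collects variables that it considers possible predictors of the primary outcome, and it already intends to model them together with treatment group. With a binary outcome and 150 per arm, leaving out predictive covariates costs some precision. It also means that a chance difference between the arms in, say, nicotine dependence is not accounted for in the estimate. The Discussion says that many smokers must be screened to find enough eligible ones, so precision obtained without recruiting anyone is worth having.

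There is also a pre-specification issue. The secondary model will itself yield an adjusted treatment coefficient for the primary outcome, from an open-ended covariate list. If the crude and adjusted results differ, the text does not say what role the adjusted one has.

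**Working it through.** **1. Reproduce the plan's sample size.** Inputs from Sample size calculation: rates 0.35 and 0.20, and "putting the risk of a type I-error at 5% and the risk of a type II-error at 20" per cent. I took alpha as two-sided, which the text does not state but which reproduces its figure. The unpooled formula is

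n = (1.960 + 0.842)² × (0.35×0.65 + 0.20×0.80) / 0.15² = 7.849 × 0.3875 / 0.0225 = 135.2, rounded up to 136.

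This matches the stated 136; the pooled formula gives 138. Then 136/0.9 = 151.1 against the stated 150, a difference of no consequence here. The trial is therefore sized for a comparison of two raw proportions, which is what the chi-square test does.

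**2. Power of the planned test.** With pooled rate 0.275:

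z = [0.15×√150 − 1.960×√(2×0.275×0.725)] / √0.3875 = (1.837 − 1.238)/0.622 = 0.963, so power is 83.2%.

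At 136 per arm it is 79.4%.

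**3. Power with adjustment.** Simulation settings: 4,000 trials per row, Monte Carlo standard error about 0.6 points for each power, marginal rates 35% and 20%, and five independent covariates of equal weight. The comparison is chi-square against the likelihood-ratio test for treatment in the adjusted logistic model. AUC and R² describe how well the covariates jointly predict abstinence. They are **assumed**, because the documents give no value.

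| AUC (R²) | 150/arm: chi-square | 150/arm: adjusted | 136/arm: chi-square | 136/arm: adjusted |
|---|---|---|---|---|
| 0.50 (0) | 82.9% | 83.5% | 79.7% | 79.5% |
| 0.58 (0.014) | 83.7% | 83.7% | 79.7% | 80.8% |
| 0.64 (0.04) | 83.9% | 85.6% | 80.3% | 82.7% |
| 0.68 (0.07) | 82.7% | 85.7% | 81.3% | 84.1% |
| 0.75 (0.13) | 83.5% | 88.8% | 80.9% | 86.0% |

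At 150 per arm the gain is 0.0, 1.7, 3.0 and 5.3 points in rows two to five. Row one, where there is nothing to gain, differs by 0.6 points, so gains of that size are noise.

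**4. Analytic check.** Replace n by n/(1−R²). At 150 per arm, R² = 0.05 gives 85.1% and R² = 0.10 gives 86.9%, against 83.2% unadjusted. In participants, R² of 0.04, 0.07 and 0.13 is worth 150/0.96 − 150 ≈ 6, 150/0.93 − 150 ≈ 11 and 150/0.87 − 150 ≈ 22 extra per arm.

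**5. Type I error.** With no treatment effect (20% in both arms), the simulated error was 4.5 to 5.4% for chi-square and 4.3 to 5.8% for the adjusted test. Both are about nominal.

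**6. Can the data carry five covariates?** Expected quitters are 150×0.35 + 150×0.20 = 82.5. Treatment plus five covariates is six coefficients if each covariate takes one, so about 14 quitters per coefficient.

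**7. Sensitivity to the missing-as-smoker rule.** Suppose (an assumption) that 35% and 20% are rates among those followed, and that 10% are lost and counted as smokers. The analysed rates become 31.5% and 18.0%, and chi-square power at 150 per arm is 77.6%. On the n/(1−R²) approximation, 80% is regained when 150/(1−R²) reaches about 159, that is at R² of about 0.06.

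**The case against.** The case for leaving the plan alone is good, and most of it stands.

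- **Validity.** A reader might infer that the chi-square is biased or wrong because it ignores baseline differences. The documents do not support that. Under randomisation the crude comparison is unbiased, and its error rate already allows for chance imbalance. Since no stratification factor is named, no design factor has been left out of the analysis.
- **Strength of the predictors.** A reader might infer that strong predictors are being thrown away. The Data analysis section calls them only candidates, and Hypothesis and research questions leaves it open which characteristics predict outcome. Entry is limited to motivated smokers with mild to moderate airflow limitation, which may narrow the prognostic spread. The gain could be close to nil.
- **Power.** A reader might infer that the trial is underpowered for want of adjustment. On the plan's own rates it is not: 83.2% exceeds the 80% target. The 77.6% in step 7 depends on a reading of the rates that the text does not settle, and it arises from the missing-data rule, not from the choice of test.
- **Effect estimate.** It is tempting to add that a chi-square test gives no estimate or interval. That is a reporting detail which an article may leave to the full analysis plan, and the 15-point scale is already set.
- **Overlap with secondary question 1.** That model will contain an adjusted treatment coefficient. This is true, but it is built to find predictors, its covariate list is open, and it is not designated as an analysis of the treatment effect.

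What remains is that a better use of data already in hand is available at almost no cost, and that it concerns a method the article states, not a detail it omits.

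**Conclusion.** The point holds as an optional efficiency and pre-specification improvement of minor weight. At 150 per arm, adjustment should bring about 0 to 3 points of power for weak to moderate predictors (AUC up to about 0.68) and about 5 points if they are strong (AUC about 0.75). It also accounts for chance imbalance in the variables adjusted for; it does not correct a bias. The direction is secure if the covariates predict abstinence at all. The size is not secure, because it rests on assumed AUC values and on simulated independent covariates of equal weight. The planned test meets its own target if 35% and 20% apply to all randomised participants. If they apply only to those followed, the same small gain could decide whether 80% is reached.

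**What to change.** In Data analysis, replace the sentence on the primary test with wording to this effect:

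- The primary analysis is a logistic regression of 12-month prolonged abstinence on treatment group (experimental group against control group 1), adjusted for a short list fixed before data lock. An example list is FTND score, previous quit attempts, age, sex and baseline FEV1 % predicted.
- The result is reported as a standardised (marginal) risk difference with 95% CI. This keeps it on the 15-point scale of the sample size calculation; the model's own odds ratio is conditional on the covariates and does not. Say which quantity carries the primary p-value.
- The chi-square test is kept as a supporting analysis.
- Covariates are not chosen from the results of secondary question 1.
- A simple rule for missing baseline values is stated, so that every randomised participant stays in the analysis. FEV1 is needed for eligibility and should be complete; questionnaire items such as the FTND are where gaps are likelier.

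The cost is wording only. No new data, visits or participants are needed, and the sample size can stand. The downsides are the extra missing-value rule and a result that takes a little more explanation than two raw percentages.

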### In- and exclusion criteria and process of eligibility screening

Eligibility is screened in two steps; during an initial telephone interview followed by spirometry. The following inclusion criteria are checked during the telephone interview: smoking history of 10 or more pack years; being motivated to stop smoking; being competent to read and speak Dutch; and reporting a respiratory symptom, defined as an affirmative answer to at least one of the following three questions: "Do you cough regularly?", "Do you cough up phlegm (sputum) when you don't have a cold?" or "Have you been shorter of breath lately?". Exclusion criteria are: evidence of a prior respiratory diagnosis, defined by an affirmative answer to the question "Do you have COPD, chronic bronchitis, asthma or asthmatic bronchitis?". Participants are also not allowed to have undergone a lung function test (spirometry) during the preceding 12 months. One or more contraindications for using the smoking cessation medication (nortriptyline) are also reasons for exclusion, among others the current use of anti-depressants. Nortriptyline is a tricyclic anti-depressant which should not be used for smoking cessation in conjunction with another anti-depressant. After the end of the telephone interview, an appointment for spirometry at Medical Centre Annadal is scheduled. Subjects are eligible for participation who have airflow limitation defined as post-bd. FEV_1_/FVC < 70% in combination with post-bd. FEV_1_≥ 50% of predicted value; i.e. mild (GOLD 1) or moderate (GOLD 2) airflow limitation, according to the international GOLD guideline [1]. The results of spirometry are not discussed during or directly after spirometry.

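### The day-50 regression of mood on abstinence (secondary analysis 2) has no treatment-group term and falls at the end of an antidepressant course assigned to the two nurse arms only, so a small part of any association may be due to the drug

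*Protocol article*

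**What the plan says.** **Drug.** Under In- and exclusion criteria the article states: "Nortriptyline is a tricyclic anti-depressant which should not be used for smoking cessation in conjunction with another anti-depressant". The section on use of nortriptyline assigns it to two of the three arms: "Participants from both the experimental group and control group 1 receive an equal dosage of nortriptyline". Intake starts on day 1, and the course runs to day 49: "As from day 8 through the end of the treatment period (day 49), participants take 75 mg a day". The dose may be reduced or stopped for side-effects. At the next visit: "At the first follow-up visit (day 50) the RA collects and counts the remaining pills". Control group 2 is not assigned the drug, but the Discussion expects its participants to ask their GP for it.

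**Measurement.** Table 1 (Data collection) schedules BDI and HADS at baseline and at days 50, 197 and 379. Questionnaires are completed at home and handed in at the visit.

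**Analysis.** Secondary analysis 2 regresses the health measures, including "quality of life, and mental health on abstinence at each follow-up visit using linear regression models". It names no treatment-group or drug term. Secondary analysis 1, listed just before it, does say that treatment group is controlled for. Secondary question 2 itself (Hypothesis and research questions) asks about effects at 12 months.

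**Labelling.** Secondary analysis 4 uses only the two nurse arms and says: "The outcome variable in these analyses is abstinence from smoking at the first follow-up visit".

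**The concern.** Randomisation balances the arms. It does not balance abstainers against smokers. At day 50 the two nurse arms have both the higher expected quit rate and an antidepressant just completed. An antidepressant can plausibly improve depression and anxiety scores whether or not the person has stopped smoking. In a regression without an arm term, abstainers are over-represented among those assigned the drug, and a mood difference due to the drug would be read as an effect of quitting.

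Within the nurse arms there is a second possible route. Drug intake can vary, and if those who stay abstinent also take more tablets, an arm term would not remove that part.

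The risk is that the trial credits quitting with an early mood benefit that belongs partly to the tablets. Equal dosing in the two nurse arms protects the primary comparison, but not this one.

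**Working it through.** The plan gives no figure for this analysis, so there is none to reproduce. The quit rates below are those behind its 136 per group, which does reproduce: (1.960 + 0.842)² × (0.35×0.65 + 0.20×0.80) / 0.15² = 135.2, rounded up to 136.

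**Timing.** Day 1 through day 49 is 49 days, or seven weeks. The visit is 50 − 49 = 1 day after the last planned dose. Because questionnaires are filled in at home beforehand, some may be answered while tablets are still being taken. The later visits fall 197 − 49 = 148 and 379 − 49 = 330 days after the last planned dose.

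**Inputs from the article.** Abstinence of 35%, 20% and 8% (Sample size calculation); allocation 3:3:1 (Randomization), which gives 150:150:50 if the nurse arms reach 150. These are 12-month rates, used here as a stand-in for day 50.

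**Assigned exposure by smoking status.**
- Abstainers: 150×0.35 + 150×0.20 + 50×0.08 = 52.5 + 30 + 4 = 86.5. In nurse arms: 82.5/86.5 = 95.4%.
- Smokers: 97.5 + 120 + 46 = 263.5. In nurse arms: 217.5/263.5 = 82.5%.
- Gap: 12.8 percentage points.

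**Arm-level bias** = exposure gap × drug effect on the score. The drug effect is not in the documents; 0.2 to 0.5 SD is assumed. This gives 0.128×0.2 = 0.03 SD to 0.128×0.5 = 0.06 SD.

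**Sensitivity of the gap.**

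| Assumption | Exposure gap (points) | Bias at 0.2 to 0.5 SD |
|---|---|---|
| Plan's rates, no nortriptyline in control group 2 | 12.8 | 0.03–0.06 |
| 25% of control group 2 obtain it | 9.6 | 0.02–0.05 |
| 50% of control group 2 obtain it | 6.4 | 0.01–0.03 |
| Day-50 rates 50/35/15%, none in control group 2 | 14.2 | 0.03–0.07 |
| Control group 2 at its stated minimum of 32, plan's rates, no use | 8.9 | 0.02–0.05 |

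**Adherence part.** If abstainers in the nurse arms take 10 to 30 percentage points more of their tablets than smokers (assumed), the within-arm bias is 0.10×0.2 = 0.02 SD to 0.30×0.5 = 0.15 SD. An arm term does not remove it. No figure in the article supports any value in this range.

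**Labelling comparison.** Experimental group against control group 1, equal dosage: planned exposure gap of zero.

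**The case against.** **The question is posed at 12 months.** True. Day 379 is 330 days after the last planned dose, so the question as asked can be answered off the study drug. This confines the point to the intermediate day-50 result; it does not remove it, because the analysis sentence extends to each visit.

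**The sentence is ambiguous.** Table 1 measures lung function only at baseline and day 379, and MRC dyspnoea not at day 50, so a same-visit day-50 regression cannot be meant for every outcome. The phrase might describe only the abstinence predictor. BDI and HADS are collected at day 50, however, and a day-50 mood model remains the natural reading.

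**Covariates belong in the analysis plan.** Usually so. Here the same list states a treatment-group term for analysis 1 and none for analysis 2, so a reader would take the difference as intended.

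**Adherence may follow from relapse.** Someone who resumes smoking may stop the tablets for that reason. The pill count is then partly a consequence of smoking status, and adjusting for it could introduce bias. This stands, and it limits pill-count adjustment to a sensitivity analysis.

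**A stronger reading: the drug also spoils the labelling analysis.** A reader might infer this because both arms in analysis 4 take nortriptyline up to the day before its only visit. The documents do not support it. The arms are randomised and dosed equally, and the outcome is abstinence, not mood. Blunting of a distress reaction to the label is possible, but nothing in the article shows it. BDI and HADS scores from days 197 and 379 could not serve as mediators there, since they come after the day-50 outcome.

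**Conclusion.** The point holds for question 2 at day 50 only. As written, the regression compares non-randomised groups whose assigned antidepressant exposure differs by about 13 points, and no stated term separates drug from quitting. The arm-level bias is small: about 0.03 to 0.06 SD, given an assumed drug effect of 0.2 to 0.5 SD and 12-month rates standing in for day 50. It shrinks if control group 2 obtains nortriptyline, as the Discussion expects.

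A reader might infer a larger bias. With 90% of tablets taken by abstainers and 60% by smokers, for example, exposure would be 0.954×0.90 = 0.858 against 0.825×0.60 = 0.495, and the bias 0.07 to 0.18 SD. About two-thirds of that gap, (0.363 − 0.128)/0.363, comes from adherence values that have no source in the documents, so it should not be presented as the expected size.

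For labelling, the most that can be said is that any day-50 mood finding would have been observed under nortriptyline in both arms. Neither the primary comparison nor the 12-month answer to question 2 is called into doubt by the day-50 timing.

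**What to change.** In secondary analysis 2:

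1. State that the mental-health conclusions rest on BDI and HADS at day 379, supported by day 197. This matches the 12-month wording of the question.
2. Add a treatment-group term, as analysis 1 already has.
3. Report day-50 mental health descriptively, labelled as an on-drug result that cannot support a claim about quitting alone. If pill counts are used, restrict that model to the nurse arms and present it as a sensitivity analysis, with the caution that tablet intake may follow from relapse.

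For question 4, no change is needed on this account. If day-50 mood is described there, one sentence should say that both arms had been assigned nortriptyline.

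The cost is wording in the analysis plan; all the data are already collected. The downside is that day 50 no longer supports a mental-health claim about quitting.
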